**PROTOCOL SYNOPSIS**

| **Title** | **Safety and Feasibility of Allogeneic Cord Blood-Derived Cell Therapy in Preterm Infants with Severe Brain Injury** |
| --- | --- |
| **Objectives** | Primary   1. To evaluate feasibility of availability of allogeneic umbilical cord blood cells (UCBCs) in surviving preterm infants with severe brain injury. 2. To evaluate safety of administration of allogeneic UCBCs in surviving preterm infants with severe brain injury.   Secondary   - 1. To evaluate the effect of administration of allogeneic UCBCs on short and long-term clinical outcomes.   2. To evaluate the effect of administration of allogeneic UCBCs on immune responses, as measured by cytokine levels. |
| **Outcomes and outcome measures** | Primary outcomes   - 1. Feasibility: Availability of at least 4/6 HLA-matched allogeneic UCBCs sourced from the BMDI Cord Blood Bank for >60% of eligible infants.   2. Safety: Absence of serious adverse events related to UCBCs administration during and for 48 hrs post-infusion and the absence of graft versus host disease (GVHD) in the first three months after cell infusion.   Secondary outcomes   - 1. Clinical outcomes      1. Death, until 24 months of corrected age      2. Moderate to severe bronchopulmonary dysplasia, assessed at 36 weeks of postmenstrual age      3. Severe retinopathy of prematurity, assessed before discharge      4. Necrotising enterocolitis, assessed before discharge      5. Culture proven sepsis, assessed before discharge      6. Developmental delay, assessed anytime until 24 months of corrected age      7. Cerebral palsy, assessed anytime until 24 months of corrected age      8. Blindness, assessed any time until 24 months corrected age      9. Deafness, assessed any time until 24 months corrected age   2. Laboratory outcomes: Effect of allogeneic UCBCs on infant’s cytokines levels, including interleukin 1b (IL-1b), IL-6, Tumour Necrosis Factor (TNF-α), and IL-10 just before UCBC administration and 1-day and 7-day post administration |
| **Trial population** | 20 preterm infants with severe brain injury, with 10 each in each stratum (<28 weeks, ALLO-1 trial and 28-37 weeks, ALLO-2 trial), will be enrolled to receive UCBCs, if appropriate matching is achieved |
| **Description of sites enrolling participants** | This trial will only recruit participants from Monash Children’s Hospital |

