   1. ***Primary*:** To evaluate the safety and feasibility of administration of single-dose, at least 4/6 or higher HLA-matched allogeneic UCBC therapy in preterm infants with severe brain injury.
   2. ***Secondary:***
      1. To evaluate the effect of administration of allogeneic UCBCs on short and long-term clinical outcomes of enrolled preterm infants.
      2. To evaluate the effect of administration of allogeneic UCBCs on immune responses as measured by cytokine levels in enrolled preterm infants.
2. **METHODS**
   1. ***Design***

This is an open-label, phase-I, single-arm, feasibility, and safety study.

- 1. ***Setting***

The studies will be conducted at Monash Newborn, Monash Children’s Hospital, and Monash Medical Centre, Monash Health, in partnership with BMDI Cord Blood Bank, Parkville and Hudson Institute of Medical Research, Clayton.

- 1. ***Ethics***

The study will be conducted in compliance with the approved protocol/amendment(s), conditions of Monash Health Human Research Ethics Committee **(**HREC) approval, and the NHMRC National Statement on Ethical Conduct in Human Research 2007.^27^ A letter of study approval will be obtained from HREC prior to the commencement of the trial. Further, any amendments to the study will be submitted to HREC for approval prior to being implemented.

- 1. ***Participants***
     1. Inclusion criteria
        1. Preterm infants born before 28 completed weeks of gestation (up to 27+6 weeks, ALLO-1 trial) OR born between 28 and 36+6 weeks of gestation (ALLO-2 trial) AND
        2. Severe brain injury detected on neonatal neuroimaging any time after birth. Severe brain injury will be considered as grade 3 (IVH with ventricular distension) or 4 (parenchymal haemorrhagic infarct) IVH,^28^ and diffuse white matter injury like cystic (grade 3) PVL^29^ or significant white matter loss. If there is uncertainty regarding the severity of preterm brain injury, a discussion will be conducted with the clinical and radiological teams to assess and confirm whether the injury qualifies as severe.
     2. Exclusion criteria
        1. Infants with known major congenital anomalies OR
        2. Infants whose care is being redirected to comfort care.

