Cell therapy will only be administered when preterm infants are clinically stable, which is deemed by the treating physician. Also, infants should not be receiving antimicrobial therapy for confirmed or presumed late-onset neonatal sepsis, which is active at the time of cell infusion, as their course may be unpredictable and may confound adverse events falsely attributing to the cell therapy.

- 1. ***Recruitment and identification of potential participants***

Head ultrasound or magnetic resonance imaging (MRI) scans for preterm infants admitted to the neonatal intensive care unit at Monash Children’s Hospital will be reviewed by the study team daily to identify severe brain injury. If a severe brain injury is identified on the scan, the infant’s family will be approached for consent, provided all the additional criteria are met. The eligibility will be further re-confirmed before administering the intervention.

- 1. ***Consent***

The study team will explain verbally about the trial and will also provide the Participant Information and Consent Form to the parent or legal guardian. The participant's family will be given sufficient time for consideration and family discussion for providing written, voluntary consent that is free from coercion. The team member obtaining the informed consent will also sign the informed consent form. A copy of the consent form will be given to the parent or legal guardian. Documentation about the participant’s participation and voluntary consent will be noted in the electronic medical record. Participants’ families who wish not to participate in the trial will be recorded. Similarly, eligible participants who are not approached and participants who have a severe brain injury but are otherwise ineligible will be recorded in the enrollment log.

- 1. ***Sample size***

A minimum of 20 preterm infants, with 10 each in each stratum (<28 weeks, ALLO-1 trial and 28 to 36+6 weeks, ALLO-2 trial), will be enrolled to receive UCBCs at the dose range mentioned below, if appropriate HLA matching is achieved. This sample size is consistent with other cell therapy trials in newborn infants. The number of preterm infants recruited for the safety outcome (cell infusion) may be less as some eligible infants may not suffice the criteria required for HLA matching or may not survive to receive the infusion, but the aim is to assess feasibility for at least 10 infants in each stratum.

- 1. ***Intervention details***

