     1. HLA matching: Allogeneic UCBCs will be obtained from BMDI Cord Blood Bank with an HLA matching of at least 4/6. As HLA matching and processing UCBCs may be time-consuming, the eligibility (neuroimaging) will be reconfirmed before administering the allogeneic UCBCs after successful HLA matching.
     2. Age of administration: Allogeneic UCBCs will be administered via IV infusion anytime from birth until three months of life, generally within 2-3 weeks of diagnosis of confirmed severe preterm brain injury.
     3. Cell infusion: Only one allogeneic UCBC infusion will be administered intravenously.
     4. UCBC dose: The infusion is aimed for 50 million total nucleated cells (TNCs) per kilogram of body weight will be administered. This therapeutic dose is based on preclinical^30^ and clinical studies^5,6^ of UCBC for different types of perinatal brain injury.
     5. Route: The UCBCs will be administered intravenously via a peripheral intravenous cannula.
  2. ***Comparison***

There will be no control group as this is a single-arm, open-label, phase-I study.

- 1. ***Outcomes***
     1. Primary outcomes
        1. Feasibility: Allogeneic UCBC therapy will be considered feasible if there is an availability of at least 4/6 HLA-matched allogeneic UCBCs sourced from the BMDI Cord Blood Bank for >60% of eligible infants.
        2. Safety: Allogeneic UCBCs will be considered as safe if there are no serious adverse events related to UCBCs during and for 48 hrs post-infusion and the absence of GVHD in the first three months after cell infusion. The safety outcomes will be reported for eligible infants where feasibility is demonstrated, and allogeneic UCBCs are administered.
     2. Secondary outcomes
        1. Clinical outcomes: The following clinical outcomes will be reported for the infants who received infusion.
           1. Death, until 24 months of corrected age
           2. Moderate to severe bronchopulmonary dysplasia, assessed as oxygen or positive pressure requirement at 36 weeks of postmenstrual age
           3. Severe retinopathy of prematurity, assessed as any retinopathy requiring anti-VEGF or laser treatment before discharge
           4. Necrotising enterocolitis, assessed as bell stage 2 or more before discharge
           5. Culture-proven sepsis, bacterial or fungal, requiring antibiotics treatment for 7 or more days before discharge

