The criteria for eligibility will be confirmed on the day of infusion. The cell product will be obtained from the BMDI Cord Blood Bank a day before the transfusion. CBU released from the Cord Blood Bank for this study will have undergone all pre-release testing as routinely performed for release for bone marrow transplant, and have met compliance with the AusCord Quality & Release Criteria. The CBU will be released under “Exceptional Release” and the TGA notified as the bank is not licensed for the release of unrelated allogeneic non-homologous use. The product will be thawed at Monash Health Translation Precinct's Cell Therapy and Regenerative Medicine Platform. After thawing, washing of cells (to remove DMSO, a cryopreservant) will be undertaken using Dextran-Albumin and resuspended in 4% albumin as per standard clinical practice. Cell viability (>70% viable CD34+ cells, in accordance with the AusCord Quality & Release Criteria.) will be determined before administration. UCBCs will be administered intravenously (through a peripheral intravenous catheter) within one hour of thaw at a dose of 50 million (as available in aliquot) viable TNCs/ kg body weight. The exact dose will depend on the number of viable TNCs available in the final cell product. The volume of cell infusion(s) will be 10 mL/kg, and cell infusion will occur over one hour undertaken in the neonatal unit or the clinical trials facility of Monash Children's Hospital. The custody of care of the product will be transferred from BMDI Cord Blood Bank to the shipper to Monash Health Translation Precinct's Cell Therapy and Regenerative Medicine Platform to the clinical team using appropriate standard operating procedures.

- 1. ***Statistical analysis***

Descriptive statistics will be used to report demographics and outcomes. The categorical variables will be described as frequency and percentage and continuous variables as median (interquartile range) and mean (standard deviation), depending on the normality of the data, which will be determined by the Shapiro-Wilk test. The data will be analysed using STATA Version 17.0 (StataCorp LLC, College Station, TX, USA). Paired t-tests or Wilcoxon signed-rank tests will be performed to compare the laboratory parameters before and after infusion.

- 1. **Safety monitoring and reporting**
     1. Monitoring **(Figure 1 and Table 1):**
        1. The following will be monitored during and within 48 hours of infusion.
     - During infusion

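### Moderate to severe BPD is defined only by respiratory support at 36 weeks postmenstrual age, which for the latest-born ALLO-2 infants falls in the first week of life or before birth

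*Combined protocol and SAP*

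**What the plan says.** The Protocol Synopsis lists "Moderate to severe bronchopulmonary dysplasia, assessed at 36 weeks of postmenstrual age" among the secondary clinical outcomes. Methods, Outcomes (clinical outcomes, item 2) adds the criterion: "Moderate to severe bronchopulmonary dysplasia, assessed as oxygen or positive pressure requirement at 36 weeks of postmenstrual age".

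Methods, Participants, Inclusion criteria sets the two strata as "Preterm infants born before 28 completed weeks of gestation (up to 27+6 weeks, ALLO-1 trial") and "born between 28 and 36+6 weeks of gestation (ALLO-2 trial").

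The reporting population is the same for every clinical outcome: "The following clinical outcomes will be reported for the infants who received infusion". Methods, Statistical analysis adds only that "The categorical variables will be described as frequency and percentage".

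No section gives a minimum age, a duration of support, another time point for later births, or a category for infants who cannot be assessed. In the Case Report Form, Overall outcomes during nursery stay, bronchopulmonary dysplasia is a blank line without a definition.

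**The concern.** A 36-week assessment identifies chronic lung disease only because a very preterm infant is by then many weeks old. That holds throughout ALLO-1. It fails towards the upper end of ALLO-2, where 36 weeks arrives days after birth or has already gone by. Taken literally, an infant born at 36+0 and on positive pressure that day meets the criterion for moderate to severe BPD.

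The gap looks unintended. The sepsis item in the same list requires at least 7 days of treatment, whereas the BPD item has no duration condition. Recruitment is from a neonatal intensive care unit, so respiratory support in the first days of life is foreseeable.

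What is at stake is the meaning of the reported ALLO-2 rate. The study has no control group, and describing short-term clinical outcomes is a stated secondary objective, so the definition alone tells a reader what the percentage represents.

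**Working it through.** The plan states no figure on this point, so there is none to reproduce. The check is date arithmetic.

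**Inputs.** The assessment point is 36+0 weeks = 36 × 7 = 252 days (Methods, Outcomes). ALLO-1 includes births up to 27+6 = 195 days; ALLO-2 includes births from 28+0 = 196 to 36+6 = 258 days (Methods, Participants).

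**Age at assessment** = 252 − g, where g is gestational age at birth in days.

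| Born at | g | Age at 36+0 (days) |
|---|---|---|
| 27+6 (latest ALLO-1) | 195 | 57 |
| 28+0 (earliest ALLO-2) | 196 | 56 |
| 32+0 | 224 | 28 |
| 34+0 | 238 | 14 |
| 35+0 | 245 | 7 |
| 35+1 | 246 | 6 |
| 36+0 | 252 | 0 |
| 36+1 | 253 | −1 |
| 36+6 | 258 | −6 |

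**Birth days affected in ALLO-2**
- Eligible: 258 − 196 + 1 = 63.
- Assessed at 0 to 6 days of age (35+1 to 36+0): 252 − 246 + 1 = 7.
- Born after 36+0 (36+1 to 36+6): 258 − 253 + 1 = 6.
- Together: 13/63 = 21%.

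**If 36 weeks means the completed week, 36+0 to 36+6.** The latest possible age at assessment is 258 − g. For births at 36+1 to 36+6 this runs from 5 days down to 0, so these infants can be assessed, but only in their first days. If assessment were always left to 36+6, births at 35+1 to 35+6 would be 12 to 7 days old. The first-week group would then be births at 36+0 to 36+6, which is 7/63 = 11% of days. Either way some eligible infants are assessed in the first week.

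**Effect on the rate.** One misclassified infant among n in the denominator moves the percentage by 100/n points: 10 points if n = 10, and more if fewer are infused.

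**How many infants (assumption only).** The documents give no gestation mix. Suppose a share s of 10 infused ALLO-2 infants is born after 36+0. The expected number is 10s and the chance of at least one is 1 − (1 − s)^10.
- s = 5%: 0.5 infants expected; chance 1 − 0.95^10 = 40%.
- s = 20%: 2 infants expected; chance 1 − 0.80^10 = 89%.

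**The case against.** The best defence is that little depends on this item. BPD is one of nine descriptive clinical outcomes in a single-arm phase I study, and no test or comparison between strata is planned. Few infants may be affected: the Introduction puts severe haemorrhage at 5% below 32 weeks and 11.6% below 27 weeks, which suggests that risk falls with gestation, and it gives no figure for 33 to 36 weeks. The Case Report Form also records invasive and non-invasive ventilation days, days to room air and home oxygen, so brief and prolonged support can largely be told apart. In practice a clinician would probably not call first-day support BPD.

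Most of this stands as a limit on importance. It does not repair the rule, because the written criterion still classifies such an infant as a case and the protocol expressly admits these births.

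Four stronger readings are tempting, and the documents do not support them.
- A reader might infer that unassessable infants would be counted as free of BPD, because outcomes are reported for all infused infants. The plan sets a reporting population but no scoring rule, so not applicable fits the text equally well.
- A reader might say that more than half of ALLO-2 is affected: births from 32+1 onwards are assessed before 28 days or not at all, 28 + 6 = 34 of 63 days (54%). The 28-day threshold appears nowhere in the documents, an infant assessed at 27 days is not in acute newborn distress, and birth days are not infants.
- A reader might say flatly that births after 36+0 cannot be assessed. That holds only if 36 weeks means exactly 36+0.
- A reader might treat 10 percentage points per infant as fixed. Methods, Sample size plans "A minimum of 20 preterm infants, with 10 each in each stratum (<28 weeks, ALLO-1 trial and 28 to 36+6 weeks, ALLO-2 trial"), but goes on to say that the number infused may be less.

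**Conclusion.** The concern holds for the latest-born part of ALLO-2. The definition yields a first-week assessment, or none, for 13 of the 63 eligible birth days (21%), taking 36 weeks as 36+0. Reading it as a whole week turns the missing assessments into ones made at 0 to 5 days of age, which does not make them valid for chronic lung disease. In such infants the reported BPD rate would not measure the condition it names, and the handling of any who cannot be assessed is unstated.

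This is a rule that gives the wrong answer for infants the protocol admits, not merely a missing detail. How many infants that means cannot be determined from the documents and may be small. ALLO-1, the primary feasibility and safety outcomes, and the sample size are unaffected. The change should be made because it is simple and the outcome is otherwise hard to interpret in ALLO-2.

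**What to change.** In the Protocol Synopsis and in Methods, Outcomes:

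1. State whether 36 weeks means 36+0 or the completed week.
2. Limit the 36-week BPD outcome to infants who have reached a prespecified minimum postnatal age by then. One example is 28 days, which means born at or before 32+0. The cut-off is the sponsor's choice.
3. Report the assessable denominator for each stratum beside the BPD count.
4. Report later-born ALLO-2 infants as not applicable, or show their respiratory support at a fixed postnatal age on a separate line.

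The cost is outcome wording and one Case Report Form line. No visit, sample or procedure is added. The form already holds totals of ventilation days and days to room air, and support on a given date can be taken from the medical record.

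The drawback is a smaller ALLO-2 denominator. With the 28-day example, births from 28+0 to 32+0 remain: 224 − 196 + 1 = 29 of 63 birth days. A 7-day minimum would keep 63 − 13 = 50, but would still admit assessments as early as one week of age.

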**Overall outcomes during nursery stay**

| **Days of ventilation** | **Invasive** | | **Noninvasive** |
| --- | --- | --- | --- |
| **Days to room air** | **Home oxygen**  Y/N | | **Amount** |
| **Length of stay** | | **Referral to NDIS** | |
| **Term MRI brain** | | | |
| **Other morbidities or outcomes relevant to the study before discharge (please give details)**  **FEASIBILITY: Y/N HLA Matching: 4/6, 5/6, 6/6 HLA Loci matched:**  **SAFETY: Y/N**  **Necrotising enterocolitis**  **Culture proven late onset sepsis**  **Bronchopulmonary dysplasia**  **ROP**  **Intraventricular haemorrhage**  **Comments** | | | |
| **Neurodevelopment testing during admission**  **General Movements**  **HINE** | | | |
| **Medications on discharge** | | | |

| **Death before nursery discharge**  **Cause of death** |
| --- |

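### BPD, NEC, sepsis and treated ROP are not tied to the time of infusion, so events that predate the cells meet the secondary outcome definitions

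*Combined protocol and SAP*

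**What the plan says.** The secondary objective in the protocol's Trial Objectives is "To evaluate the effect of administration of allogeneic UCBCs on short and long-term clinical outcomes of enrolled preterm infants". The Outcomes section reports the clinical outcomes for infused infants only. It gives BPD as "Moderate to severe bronchopulmonary dysplasia, assessed as oxygen or positive pressure requirement at 36 weeks of postmenstrual age". For treated ROP, NEC (Bell stage 2 or more) and culture-proven sepsis (at least 7 days of treatment), the only time limit is discharge.

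Under Intervention details, the cells may be "administered via IV infusion anytime from birth until three months of life", and this is "generally within 2-3 weeks of diagnosis of confirmed severe preterm brain injury". The qualifying injury may be found at any time after birth. The Participants section adds that "infants should not be receiving antimicrobial therapy for confirmed or presumed late-onset neonatal sepsis, which is active at the time of cell infusion".

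No section limits these four outcomes to onset after infusion, asks for earlier episodes to be listed as baseline, or says what to do when 36 weeks postmenstrual age (PMA) comes before infusion.

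On the case report form, NEC, BPD, ROP and "Culture proven late onset sepsis" are lines in the block for the whole nursery stay, with no onset date. The first page has another culture-proven sepsis entry, also undated. The page for the day of infusion does record the date, day of life and corrected gestation.

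**The concern.** An event that happened before the cells were given cannot reflect their effect. The infusion window overlaps the period in which all four outcomes can arise, so a reported rate can mix baseline morbidity with events after treatment.

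The sepsis rule sharpens this. An infant who develops sepsis while waiting for a match is infused once treatment for it has ended. That episode, if treated for 7 days or more, then meets the outcome definition. The protocol gives avoidance of false attribution to the cells as its reason for the rule, and an outcome definition with no start point works against that precaution.

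At stake is the meaning of the short-term clinical results. There is no control group and reporting is by frequency and percentage, so the observed rate is the entire result for these outcomes.

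**Working it through.** The plan gives no figure to reproduce here. The check is date arithmetic.

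**Inputs.** From the protocol: infusion from birth to three months of life (taken as 91 days; using 90 or 92 shifts each cut-off by one day); gestation at birth up to 27+6 weeks (ALLO-1) or 28+0 to 36+6 (ALLO-2); BPD time point 36+0 weeks PMA, which is 36 × 7 = 252 days; 10 infants per stratum. The day of diagnosis is not given and is assumed below.

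**Age when the BPD time point is reached** = 252 − gestation at birth in days.
- Born 27+6 (195 days): 252 − 195 = day 57.
- Born 32+0 (224 days): 252 − 224 = day 28.
- Born 34+0 (238 days): 252 − 238 = day 14.
- Born 36+1 to 36+6 (253 to 258 days): −1 to −6, that is, 1 to 6 days before birth. No infusion can come first.

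**Outer limit of the window.** 252 − 91 = 161 days = 23+0 weeks. Any infant born at 23+0 or later reaches 36+0 PMA by day 91. A permitted infusion can therefore follow the BPD time point throughout ALLO-2 and in nearly all of ALLO-1.

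**Usual timing.** The BPD time point precedes infusion when gestation at birth exceeds 252 − infusion day. Taking lags of 14 and 21 days from diagnosis:

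| Diagnosis day (assumed) | Infusion day | 36+0 precedes infusion for births above |
|---|---|---|
| 7 | 21 / 28 | 33+0 / 32+0 |
| 28 | 42 / 49 | 30+0 / 29+0 |
| 42 | 56 / 63 | 28+0 / 27+0 |

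With diagnosis on day 7, every ALLO-1 infant is infused before 36+0. In this table ALLO-1 is reached only in the last case (diagnosis day 42, lag 21 days), for births at 27+1 to 27+6. The protocol's wording makes 2-3 weeks a usual upper bound, so shorter lags are possible and would raise these cut-offs.

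**NEC, sepsis and treated ROP.** The documents give no onset distribution, so the share of events before infusion cannot be derived. As illustration only, assume a constant hazard over a stay of L weeks and infusion in week t; the share is then min(1, t/L). With L = 14 it is 3/14 = 21%, 6/14 = 43% and 13/14 = 93% for t = 3, 6 and 13. Across L = 10 to 16 the range is 19% (3/16) to 100%. The conclusion does not rest on these figures.

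**Effect on a rate.** One event among 10 infants is 1/10 = 10 percentage points. The Sample size section allows that fewer may be infused, in which case each event weighs more.

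**Outcomes not affected.** Primary feasibility depends on match availability. The primary safety windows (48 hours and three months) start at infusion. Death can only follow infusion, because only infused infants are counted. The early neurological outcomes are set at 3-4 months corrected age. Even for a birth at 36+6, term (40+0) is day 280 − 258 = 22 and three months corrected age is about day 22 + 91 = 113, after the infusion window closes.

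**The case against.** The strongest reply is that this is a small, uncontrolled phase I study with descriptive reporting. The only before-and-after test is for laboratory parameters, and the primary outcomes are properly anchored. The form already holds date of birth, gestation and infusion date, so whether infusion preceded 36 weeks PMA can be derived for every infant. The nursery-stay block invites details and comments, the Reporting section covers any event after the therapy, and missing dates could be taken from the medical record.

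Much of this stands. It confines the problem to four secondary outcomes, and BPD needs no new date field. It does not remove the problem: the ability to split events later is not a rule to do so, and nothing links the event reports to the outcome counts.

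A reader might infer more than the documents support:
- **That the plan counts pre-infusion events, or attributes them to the cells.** It is silent on onset. The definitions admit such events, but attribution is only an inference from the word effect in the objective.
- **That term-age MRI, general movements and Hammersmith tests share the fault.** They are monitoring items, not listed secondary outcomes.
- **That nearly all infants born at 34 weeks or later are infused after the BPD time point.** This treats the usual upper bound as a fixed lag. An infant born at 34+0 reaches 36+0 on day 14, and infusion before then is allowed.
- **That the next trial's design would be misled.** No section says that these rates will be used for that.

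**Conclusion.** The point holds for BPD, NEC, culture-proven sepsis and treated ROP. As written, these outcomes are not anchored to infusion, and events that predate it can enter rates reported under an objective about the effect of the cells. Each such event is worth about 10 percentage points in a stratum of about 10.

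For births at 36+1 to 36+6 the BPD value can never follow infusion; this needs no assumption. For other births the extent depends on when injury is diagnosed and how soon infusion follows, which the documents do not fix. With diagnosis on day 7 and infusion on day 21 to 28, the affected births are those above about 32+0 to 33+0. The BPD problem thus lies mainly in ALLO-2, and ALLO-1 is affected only with late diagnosis or late infusion. How many NEC, sepsis and ROP events would fall before infusion cannot be determined from the documents.

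**What to change.** Set time zero at infusion for NEC, culture-proven sepsis and treated ROP. Count as outcomes only episodes with onset after infusion (for ROP, treatment after infusion) and list earlier episodes as baseline characteristics. Report BPD as an outcome only for infants infused before 36+0 weeks PMA, with that denominator stated, and as a baseline characteristic otherwise. Add an onset date to the case report form lines for NEC and sepsis, and a treatment date for ROP.

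The cost is a change to the outcome wording and a few date fields. The infusion date is already on the form. Sample size, treatment and visits do not change. The downside is a smaller denominator for BPD, mainly in ALLO-2.
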